# Tolerability of concurrent external beam radiotherapy and [^177^Lu]Lu-PSMA-617 for node-positive prostate cancer in treatment naïve patients, phase I study (PROQURE-I trial)

**DOI:** 10.1186/s12885-023-10725-5

**Published:** 2023-03-23

**Keywords:** Lu-PSMA, Prostate cancer, Node-positive

## Abstract

**Background:**

Prostate cancer patients with locoregional lymph node disease at diagnosis (N1M0) still have a limited prognosis despite the improvements provided by aggressive curative intent multimodal locoregional external beam radiation therapy (EBRT) with systemic androgen deprivation therapy (ADT). Although some patients can be cured and the majority of patients have a long survival, the 5-year biochemical failure rate is currently 29–47%. [^177^Lu]Lu-PSMA-617 has shown impressive clinical and biochemical responses with low toxicity in salvage setting in metastatic castration-resistant prostate cancer. This study aims to explore the combination of standard EBRT and ADT complemented with a single administration of [^177^Lu]Lu-PSMA-617 in curative intent treatment for N1M0 prostate cancer. Hypothetically, this combined approach will enhance EBRT to better control macroscopic tumour localizations, and treat undetected microscopic disease locations inside and outside EBRT fields.

**Methods:**

The PROQURE-I study is a multicenter prospective phase I study investigating standard of care treatment (7 weeks EBRT and 3 years ADT) complemented with one concurrent cycle (three, six, or nine GBq) of systemic [^177^Lu]Lu-PSMA-617 administered in week two of EBRT. A maximum of 18 patients with PSMA-positive N1M0 prostate cancer will be included. The tolerability of adding [^177^Lu]Lu-PSMA-617 will be evaluated using a Bayesian Optimal Interval (BOIN) dose-escalation design. The primary objective is to determine the maximum tolerated dose (MTD) of a single cycle [^177^Lu]Lu-PSMA-617 when given concurrent with EBRT + ADT, defined as the occurrence of Common Terminology Criteria for Adverse Events (CTCAE) v 5.0 grade three or higher acute toxicity. Secondary objectives include: late toxicity at 6 months, dosimetric assessment, preliminary biochemical efficacy at 6 months, quality of life questionnaires, and pharmacokinetic modelling of [^177^Lu]Lu-PSMA-617.

**Discussion:**

This is the first prospective study to combine EBRT and ADT with [^177^Lu]Lu-PSMA-617 in treatment naïve men with N1M0 prostate cancer, and thereby explores the novel application of [^177^Lu]Lu-PSMA-617 in curative intent treatment. It is considered likely that this study will confirm tolerability as the combined toxicity of these treatments is expected to be limited. Increased efficacy is considered likely since both individual treatments have proven high anti-tumour effect as mono-treatments.

**Trial registration:**

ClinicalTrials, NCT05162573. Registered 7 October 2021.

**Supplementary Information:**

The online version contains supplementary material available at 10.1186/s12885-023-10725-5.

## Background

In the past, prostate cancer patients with nodal metastases were not considered for curative treatment, based on the assumption that cure was neither feasible nor beneficial, based on the hypothesis that patients with lymph node metastases are affected by a systemic disease. With the introduction of molecular imaging targeting the prostate-specific membrane antigen (PSMA), the number of patients diagnosed with primary node-positive prostate cancer without distant metastasis (staged N1M0) is increasing as PSMA PET/CT allows better detection of small nodal metastases and at the same time better exclusion of distant metastases (including nodal metastases in non-standard locations) with a high positive predictive value [1, 2]. These developments are leading to higher confidence that at least some of the current prostate cancer patients staged N1M0 may not yet have systemic disease, and therefore may potentially benefit from an aggressive multimodal treatment approach. Based on this assumption, more and more N1M0 patients are now offered high-dose locoregional external beam radiation therapy (EBRT) with a boost to all visible tumour lesions in the pelvic area combined with 2–3 years concurrent and adjuvant androgen deprivation therapy (ADT). This treatment is given with the intent to cure, or if this fails to at least provide maximum disease-free and overall survival [3].

Despite the improvements provided by aggressive multimodal locoregional EBRT with systemic long-term ADT, patients with N1M0 disease still have a suboptimal prognosis. Although the majority of patients have a long survival, curation is not always achieved and the 5-year (biochemical) failure rate is currently reported at 29–53% [4, 5]. In addition, patients receiving this treatment may experience a combination of toxicities, which may be persistent with potential impact on their remaining life. These disadvantages may be additional to surgical toxicity for patients who were staged N1 using lymph node dissection (LND) or sentinel node procedure (SNP) [6]. In combination, the current treatment with pelvic EBRT + ADT leads to many patients experiencing potentially significant reductions in quality of life (QoL), while still being confronted with recurrent and incurable disease within their remaining life. A new treatment strategy for these patients, which improves their chance of cure but also reduces toxicity and avoids reductions in QoL, is eagerly awaited.

Unfortunately, options are limited. Dose escalation of EBRT for prostate cancer is difficult due to toxicity in regional organs at risk. There are several new pharmaceutical options to intensify systemic ADT, but this has not been proven effective for primary treatment of N1M0 patients and it would likely increase long-term toxicity. The same is true for adding systemic chemotherapy, which was demonstrated to be not beneficial for low-volume metastatic patients and would also contribute to unwanted toxicity [7]. There are several directions to explore for further improvement of treatment. Firstly, current EBRT could be enhanced to better control macroscopic tumour in the prostate and detected involved nodes, secondly, undetected microscopic disease locations inside and outside EBRT fields need to be targeted with more efficacy, and, lastly, it could be beneficial to potentially shorten or obviate the long-term ADT with its associated poor QoL.

Radionuclide therapy using PSMA-ligand labelled with [^177^Lu]Lutetium-PSMA ([^177^Lu] (Lu-PSMA) may provide the desired improvements. Intravenous administration of [^177^Lu]Lu-PSMA leads to highly selective accumulation in tumour cells, and highly selective dose deposition within tumour locations. The short path length of the emitted electrons of about 1.5 mm contributes to low dose deposition in surrounding normal tissues, but still allows cross-fire and bystander effects in adjacent PSMA-negative tumour cells. This is notably not limited to known macroscopic (visible) lesions, that are detectable with e.g. a PET-scan, but it theoretically also includes undetected microscopic PSMA-positive tumour locations throughout the body. [^177^Lu]Lu-PSMA-617 therapy has already shown impressive clinical and biochemical responses with low toxicity in palliative setting in metastatic castration-resistant prostate cancer (mCRPC) (Fig. 1) [8, 9]. The recently published VISION study has shown complete biochemical response in 9.2% (17/184) mCRPC patients and PSA-decline of 50% or more in 41.8% (77/184) of the mCRPC patients receiving up to six cycles of [^177^Lu]Lu-PSMA-617 [8].

**Fig. 1 Fig1:**
[figure not shown]
Example of response of [^177^Lu]Lu-PSMA-617 in a patient with metastatic castration-resistant prostate cancer. On the left side you see a [^68^ Ga]Ga-PSMA-11 PET maximal intensity projection (MIP) of a patient with metastatic prostate cancer in bone and lymph nodes. There is physiological accumulation in the salivary glands, kidneys, spleen, and to a much lower extent small and large bowel. On the right you also see a [^68^ Ga]Ga-PSMA-11 PET MIP from the same patient after two cycles of [^177^Lu]Lu-PSMA-617 which shows almost complete response

In case of high tracer accumulation in the primary tumour and nodal metastases, a similarly high dose delivery and good anti-tumour effect could be expected in the curative setting. In combination with EBRT and ADT, the concurrent and synergistic dose delivery could enhance EBRT to better control macroscopic tumour in the prostate and detected involved nodes, and it could also treat undetected microscopic disease locations inside and outside EBRT fields.

This study aims to explore the tolerability of the combination of standard EBRT and ADT complemented with a single administration of [^177^Lu]Lu-PSMA-617, for patients who are treated with curative intent for N1M0 prostate cancer.

## Method

### Study design and subjects

The PROQURE-I study is a national multicenter prospective phase I dose-escalation study investigating the addition of one cycle of systemic [^177^Lu]Lu-PSMA-617 (Pluvicto™, Advanced Accelerators Applications) concurrent with standard of care treatment (7 weeks EBRT and 3 years ADT), in treatment naïve patients with PSMA-positive N1M0 prostate cancer (see Fig. 2). Detailed inclusion and exclusion criteria of the subjects are listed in Table 1.

**Fig. 2 Fig2:**
[figure not shown]
Study design. At the start of the treatment patients receive adjuvant hormone therapy (ADT) at most one month prior to the start of external beam radiation therapy (EBRT) and will continue during EBRT. Adjuvant hormone therapy is then continued as adjuvant treatment up to the advised total duration of 3 years (provided that its toxicity remains acceptable). In week two of EBRT, patients also receive one concurrent cycle of systemic [^177^Lu]Lu-PSMA-617 (Lu-PSMA) as part of the study procedure

**Table 1 Tab1:** Inclusion and exclusion criteria

Inclusion criteria	Exclusion criteria
Histologically proven prostate cancer	Inability to comply to study procedures
cT2-4, partly determined by MRI	Inability to adhere to radiation safety measures in hospital or at home
N1, determined by LND/SNP and/or PSMA PET/CT	Inability to undergo the required biodistribution scans
iM0, determined by PSMA PET/CT	Prior or current malignant disease with potential impact on treatment outcome or survival
Accepted for curative intent treatment with EBRT of the prostate and regional nodes + three years ADT	Prior treatment with EBRT
Visually PSMA-positive primary tumour and nodes, largest lesion > average liver accumulation	Prior treatment with ADT, already initiated > one month before the start of EBRT
WHO performance score 0–1	Prior treatment with radionuclide therapies, [^177^Lu]Lu-PSMA-617 or other
Age > 18 years	Reduced bone marrow reserve (Hb < 6 mmol/L, Leukocytes < 2.5 10E9/L, or Platelets < 100 10E9/L not older than one month before start of EBRT)
For patients who have partners of childbearing potential: Willingness to use a method of birth control with adequate barrier protection during the study and for six months after the study drug administration	Reduced renal function (GFR < 60 ml/min/1,73m^2^ not older than one month before start of EBRT)
Signed written informed consent	Reduced salivary gland function (history of prior salivary gland disease)
	Urinary problems requiring pre-treatment with ADT^a^

*ADT* Androgen deprivation therapy, *CT* Computed Tomography, *EBRT* External beam radiation therapy, *GRF* Glomerular filtration rate, *Hb* Hemoglobulin, *LND* Lymph node dissection, *Lu-PSMA* Lutetium PSMA, *MRI* Magnetic resonance imaging, *PET* Positron emission tomography, *PSMA* Prostate specific membrane antigen, *SNP* Single node procedure, *WHO* World health organization

^a^to avoid diminished PSMA- expression or escalating radiation safety issues with radioactive urine at the time of [^177^Lu]Lu-PSMA-617

### Hypothesis

The hypothesis of this phase I study is that combining EBRT and ADT (in accordance to current standard of care) with one cycle of systemic [^177^Lu]Lu-PSMA-617 delivered in week two of EBRT, in treatment naïve patients with PSMA-positive N1M0 prostate cancer will not induce significant additional toxicity. It is important to exclude significant additional toxicity, because this could potentially lead to interruption of the standard curative intent treatment. To evaluate toxicity of a multimodal treatment, the toxicities of the separate components need to be considered.

The toxicity profile of ADT has been reported extensively, and includes e.g. fatigue, sexual dysfunction, gynecomastia, flushes and depression [10]. Beyond these acute issues, there is increasing awareness of the long-term effects. ADT leads to adverse changes in body weight, body composition, insulin resistance and serum cholesterols, together known as the “metabolic syndrome”, with changes already observed after only 12–24 weeks and largely persistent after the end of treatment [11].

The acute toxicity of EBRT of the prostate and pelvic nodes with concurrent ADT has also been reported extensively, for example in the PIVOTAL study in 2018 [12]. These data illustrate that grade 1–2 acute toxicities according to Radiation Therapy Oncology Group (RTOG) criteria are common, occurring in up to 30% for the gastrointestinal tract and up to 40% for the bladder, with their peak incidence at the end of EBRT. However, grade three acute toxicities are rare, below five % in all treatment weeks for all evaluated parameters. The late toxicity of pelvic EBRT was also reported in the same study [12], which reports that occurrence of late grade one toxicities according to CTCAE criteria are common, occurring in up to about 70% for the gastrointestinal tract as well as the bladder. Late grade two toxicities are rare, below 20% up to 2 years for the gastrointestinal tract and below 30% up to 2 years for the bladder. CTCAE grade one toxicities increase during at least 2 years after treatment, and their incidence at 6 months should be considered a relatively poor indicator. Whilst grade two toxicities show much less increase over time, and their incidence at 6 months is a reasonable indicator for toxicity later on. Finally, late grade three toxicities hardly occurred (< 5%).

[^177^Lu]Lu-PSMA-617 is considered a low toxicity treatment. Renal clearance of [^177^Lu]Lu-PSMA-617 from the circulation occurs rapidly, stimulated by standard good hydration, thus blood concentrations are low. Dosimetry data have indicated that binding occurs in PSMA-expressing normal tissues (besides tumours), which mainly include the salivary glands, kidneys, and to a much lower extent small and large bowel [13]. A study using six cycles of 6–9 GBq [^177^Lu]Lu-PSMA-617 reported grade one xerostomia in 87%, grade 1–2 transient nausea in 50%, grade 1–2 fatigue in 50%, and grade 3–4 thrombocytopenia in 13% of patients [14]. As expected, studies that applied only one or two cycles [^177^Lu]Lu-PSMA-617 reported much lower toxicity rates; xerostomia (8.7%), mild nausea (12.5%), fatigue (17.4%), no CTCAE grade 2–3 thrombocytopenia, and no grade four adverse events [9].

Based on these patterns we hypothesize that tolerability of EBRT and ADT will not be affected by adding one administration of up to nine GBq [^177^Lu]Lu-PSMA-617. The toxicity of ADT is considered to be largely independent of ionizing radiation, and is not expected to change in the scope of combining EBRT with [^177^Lu]Lu-PSMA-617. The dose distributions from EBRT and [^177^Lu]Lu-PSMA-617 will have a desired overlap in tumour locations in the pelvic area, but they have no significant overlap in the dose delivered to organs at risk and there is no overlap in their toxicity profiles. Most importantly, EBRT to the pelvic area does not involve any dose to the kidneys or the salivary glands. Vice versa, [^177^Lu]Lu-PSMA-617 does not have known bladder toxicity, and no gastrointestinal toxicity beyond transient nausea after infusion. Concurrent dose delivery from EBRT and unbound [^177^Lu]Lu-PSMA-617, for example to the bladder wall (from radioactive urine passing through) and to perfused organs in the pelvic area, can be minimized by administering the radiopharmaceutical shortly after an EBRT fraction to allow about 20 h to clear the urological tract and circulation before the next EBRT fraction is delivered.

Based on these considerations, the risk of significant extra toxicity due to the addition of one cycle of [^177^Lu]Lu-PSMA-617 concurrent with EBRT and ADT is considered limited, including for higher dose levels. The occurrence of significant additional toxicity can be evaluated by monitoring (treatment related) acute CTCAE v. 5.0 grade three or higher toxicity of any type during treatment, and late CTCAE v. 5.0 grade three or higher toxicity of any type at 6 months after treatment.

### Primary objectives

To determine the maximum tolerated dose (MTD) of one cycle [^177^Lu]Lu-PSMA-617 (three, six, or nine GBq) when administered in combination with standard EBRT and ADT. MTD will be determined according to the Bayesian Optimal Interval (BOIN)-design (see section 2: Dose escalation) [15]. Dose-limiting toxicity (DLT) is defined as an acute toxicity, occurring from the start of EBRT up to 3 months after completion of EBRT, according to CTCAE v. 5.0 grade three or higher of any type. As CTCAE grade three or higher toxicities are very limited in EBRT and ADT combination therapy, this is considered to be a suitable endpoint for tolerability in this study (see hypothesis above). Relation of acute CTCAE grade three toxicity or higher to the study treatment is determined by the principal investigators, and will be verified by a safety committee prior to escalation to a higher dose level.

### Secondary objectives

Five secondary objectives have been defined: first, late toxicity CTCAE v 5.0 grade three or higher will be evaluated at 6 months post-treatment. Second, dosimetric efficacy will be assessed using the summed EQD2 dose to screen for superiority of delivered dose to tumour (and organs at risk), as compared to EBRT alone. Third, anti-tumour efficacy will be assessed using the prostate-specific antigen (PSA) response level. This parameter cannot be used to detect improved anti-tumour effect for the experimental combined treatment, but it can be used to detect a (highly unlikely) reduced anti-tumour effect. Fourth, the feasibility of QoL evaluation by using QLQ-C30 and prostate-specific QLQ-PR25 questionnaires for this specific patient group will be determined. Lastly, pharmacokinetic modelling will be used to further explore the selected dose levels and the kinetics of [^177^Lu]Lu-PSMA-617 as compared to monotherapy. Sequential blood samples before and after treatment will be combined with three time point SPECT/CT and planar whole-body biodistribution imaging to generate a pharmacokinetic model for [^177^Lu]Lu-PSMA-617 in the presence of continued fractionated EBRT.

### Investigational medicinal product

The radiopharmaceutical [^177^Lu]Lu-PSMA-617 (Pluvicto™, Advanced Accelerators Applications) is comprised of the isotope lutetium-177 ([^177^Lu]Lu) linked to a small molecule targeting the PSMA receptor. The beta-emitting [^177^Lu]Lu has a physical half-life of 6.6 days, medium-energy beta-emission (490 keV), and a maximum electron tissue path length of about 1.5 mm [16]. [^177^Lu]Lu-PSMA-617 is considered a low toxicity treatment based on previous prospective clinical trials (see also section hypothesis) [8, 14].

### Estimated total dose

The respective doses from the two different modalities need to be considered to provide an estimation of the total delivered dose.

First, EBRT physical doses can be converted to doses equivalent for two Gy fraction using the α/β (alpha/beta, fractionation sensitivity) factor. The α/β for prostate cancer has been estimated from very low (1.2) to medium (4.9) in various studies [17, 18]. In the scope of this study an intermediate α/β of three is assumed. This leads to radiobiologically equivalent doses (as delivered in two Gy fractions, EQD2_a/b3_) of 80 Gy to the prostate, 56 Gy to macroscopic nodal metastases, and 47 Gy to microscopic nodal metastases in the elective fields (Table 2).

**Table 2 Tab2:** Total dose for concurrent EBRT with [^177^Lu]Lu-PSMA-617, estimated for various tumour locations and for various [^177^Lu]Lu-PSMA activity levels

Tumour dose in Gy (EQD2)	EBRT	3 GBq [^177^Lu]Lu-PSMA-617			6 GBq [^177^Lu]Lu-PSMA-617			9 GBq [^177^Lu]Lu-PSMA-617		
**Tumour location**	**Alone**	**Alone**	**Sum**	** + 6%**	**Alone**	**Sum**	** + 6%**	**Alone**	**Sum**	** + 6%**
Primary tumour	80	6	86	**91**	12	92	**98**	18	98	**104**
Macroscopic nodes in boost field	56	9	65	**69**	18	74	**78**	27	83	**88**
Microscopic nodes in elective field	47		56	**59**		65	**69**		74	**78**
Microscopic lesions outside fields	0		9	**9**		18	**18**		27	**27**

Values are expressed in Gy (EQD2), calculated with α/β = 3 for (metastatic) prostate cancer. The column marked + 6% includes an assumed synergistic effect for tumour locations that receive dose from the combined treatments

*Lu-PSMA* Lutetium PSMA, *PSMA* Prostate specific membrane antigen

Second, [^177^Lu]Lu-PSMA-617 delivers dose to tumour with a low dose-rate over a period of ~ 3 weeks, which has been estimated at about 2.5–3.5 Gy per administered GBq depending on the tumour location [19]. For primary tumours the tracer accumulation may be more variable, and is generally lower than metastatic locations that typically consist of selected poorly differentiated and highly PSMA-expressing tumour cells. For this study, which selectively includes patients with relatively high PSMA-expression in all known lesions, we will assume a delivered dose of two Gy/GBq to the primary tumour, and three Gy/GBq for all other tumour locations.

On top of added dose, concurrent dose delivery by EBRT and [^177^Lu]Lu-PSMA-617 can provide synergetic effects that have been suggested conservatively in the range of 6% for low α/β tumours like prostate cancer [20]. Based on these considerations, we estimate that administration of one single dosage of [^177^Lu]Lu-PSMA-617 during the second week of EBRT would translate to the total doses listed in Table 2.

### Recruitment

Patients will be identified at multidisciplinary uro-oncology tumour boards, at the time of confirmed PSMA-positive prostate cancer, staged N1M0, and referred for EBRT and ADT. When patients accept EBRT and ADT, they are subsequently informed about this study. Patients will receive oral and written information from their treating physician, and will be given at least 72 h to consider participation in the study. Patients who agree to participate will sign the informed consent form. Patients who decline participation will receive standard of care treatment (EBRT and ADT).

### Time schedule

Recruitment has started in January 2022 and is expected to complete before July 2023.

### Withdrawal of individual patients

Subjects can leave the study at any time for any reason if they wish to do so without any consequences. The investigator can decide to withdraw a subject from the study for urgent medical reasons. Patients withdrawn from the study will continue to receive the standard of care treatment and follow-up as deemed appropriate by the treating physician and according to current clinical protocol. This includes evaluation and management of relevant toxicities. No additional follow-up is required.

### Dose escalation

This study will use a Bayesian Optimal Interval design (BOIN design) with a target dose-limiting toxicity (DLT) rate of 30% and three pre-specified activity levels [15]. The three pre-specified activity levels of the [^177^Lu]Lu-PSMA-617 administration are: level one: three GBq, level two: six GBq and level three: nine GBq. Planned enrolment of a maximum of 18 patients or fewer (depending on the observed rate of DLTs) will be used to evaluate safety and tolerability. The DLT rate is calculated as the number of patients experiencing a DLT during the current dose divided by the total number of patients treated at the current dose.

To accelerate dose escalation, based on the knowledge of limited toxicity with a single administration [9], the trial starts with a cohort size of one patient per activity level. A cohort is expanded to three patients if the first DLT is observed. If no DLT is observed at activity levels one and two, the cohort size at the highest activity level (level three) will also be expanded to three patients. If no DLT is observed at all, the trial is terminated at the last activity level if the upper limit of the 95% binomial confidence interval (CI) is below 0.5 and the last activity (level three: nine GBq) is then selected as the MTD. This means that when zero out of six patients have a DLT at activity level three, the trial is terminated, because the 95% CI then ranges from zero to 0.46.

If a DLT is observed, the decision to expand the cohort and retain the current activity, to de-escalate, to escalate or to stop the trial is based on the pre-specified activity escalation and de-escalation boundaries for a DLT rate of 30% (λe = 0.236, λd = 0.358) and maximum sample size according to the BOIN design principles. The resulting decision rules are presented in Table 3. In addition to these decision rules, the following rules for safety are embedded. In level one, the trial will be stopped for safety if 2/3 or 3/3 patients experience a DLT. In activity level two and three, the activity will be eliminated according to the rules specified in the last row of Table 3. Elimination of a activity indicates that the current activity and higher activities will not be investigated anymore and the trial continues on a lower activity level.

**Table 3 Tab3:** Escalation, de-escalation, elimination and stopping boundaries for each level depending on the number of patients with DLT

Action	**The number of patients treated at each dose**																	
	**1**	**2**	**3**	**4**	**5**	**6**	**7**	**8**	**9**	**10**	**11**	**12**	**13**	**14**	**15**	**16**	**17**	**18**
Level 1:																		
Stop the trial if # of DLT > =	NA	NA	2	3	3	4	4	4	5	5	6	6	6	7	7	7	8	8
Level 2 and 3:																		
Escalate if # of DLT < =	0	0	0	0	1	1	1	1	2	2	2	2	3	3	3	3	4	4
De-escalate if # of DLT > =	1	1	2	2	2	3	3	3	4	4	4	5	5	6	6	6	7	7
Eliminate dose if # of DLT > =	NA	NA	3	4	5	5	6	6	7	7	7	8	8	9	9	10	10	11

*DLT* Dose limiting toxicity, *NA* Not applicable, # number

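### A DLT in the first 6 GBq patient has two stated actions (the text expands the cohort to three, Table 3 de-escalates), and the article does not say which prevails

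*Protocol article*

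**What the plan says.** All of this is in the protocol article, Method, Dose escalation, unless noted.

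- The design is BOIN with a "target dose-limiting toxicity (DLT) rate of 30% and three pre-specified activity levels" (3, 6 and 9 GBq). The boundaries are those for a "DLT rate of 30% (λe = 0.236, λd = 0.358").
- Second paragraph: to speed up escalation, "the trial starts with a cohort size of one patient per activity level". The next sentence reads "A cohort is expanded to three patients if the first DLT is observed". It makes no exception by level. The same paragraph sets a cohort of three at level 3 when levels 1 and 2 are free of DLTs.
- Third paragraph: the sentence that opens "If a DLT is observed, the decision to expand the cohort and retain the current activity, to de-escalate, to escalate or to stop" makes that choice follow the boundaries, and "The resulting decision rules are presented in Table 3".
- Table 3 is indexed by patients treated at a dose, from 1 to 18. For levels 2 and 3, the row that begins "De-escalate if # of DLT >" (read as greater than or equal to) shows 1 at n = 1, 1 at n = 2 and 2 at n = 3. The elimination row for these levels and the level 1 stopping row show NA at n = 1 and n = 2.
- Temporary inclusion stop: enrolment pauses after the last patient of each cohort until one month after that cohort's last EBRT.

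**The concern.** Cohorts start at one and enrolment pauses after each cohort, so a decision is taken after the first patient at 6 GBq. If that patient has a DLT, the second paragraph keeps 6 GBq for two more patients. The third paragraph makes expansion itself a boundary decision, and Table 3 at n = 1 sends the trial down to 3 GBq. Two centres or two committee members applying the same page could therefore treat the next patients at different activities. The MTD is the primary objective, so the route to the primary result depends on which sentence is followed. The Monitoring section classes the study as high-risk, and this would be its first decision after a DLT.

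**Working it through.** **1. Are the table entries genuine?** Tables extracted from a PDF can be damaged, so I rebuilt the rows. Inputs: target φ = 0.30 (article), and the usual BOIN defaults φ1 = 0.6φ = 0.18 and φ2 = 1.4φ = 0.42 (assumed; the article does not state them).

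- λe = ln[(1−φ1)/(1−φ)] / ln[φ(1−φ1)/(φ1(1−φ))] = ln(0.82/0.70) / ln(0.246/0.126) = 0.2365
- λd = ln[(1−φ)/(1−φ2)] / ln[φ2(1−φ)/(φ(1−φ2))] = ln(0.70/0.58) / ln(0.294/0.174) = 0.3585

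These match the stated 0.236 and 0.358. Escalating at floor(nλe) and de-escalating at ceil(nλd) reproduces all 36 entries of the two rows. At n = 1, ceil(0.3585) = 1, so the 1 in that cell is the true boundary.

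**2. The two rules applied to one event.** The article defines the DLT rate as DLTs divided by patients treated at the current dose. One DLT in one patient is 1/1 = 1.00, above 0.358.

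| Rule | Action at 1 of 1 on 6 GBq |
|---|---|
| Second paragraph | Two more patients at 6 GBq, then the boundaries at n = 3 |
| Third paragraph with Table 3 | De-escalate to 3 GBq |

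Under the first rule, Table 3 at n = 3 gives: 1/3 = 0.333, between the boundaries, stay; 2/3, de-escalate; 3/3, eliminate. The chance that neither added patient has a DLT, so that the trial stays at 6 GBq, is (1−p2)²: 81% at p2 = 0.10, 64% at 0.20, 49% at 0.30 and 36% at 0.40. Under the second rule the next patient is treated at 3 GBq in every case.

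**3. How often does it arise?** It needs no DLT in the single 3 GBq patient and a DLT in the first 6 GBq patient: (1−p1)·p2. The rates are assumed.

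| p1 (3 GBq) | p2 (6 GBq) | Probability |
|---|---|---|
| 5% | 5% | 0.95 × 0.05 = 4.75% |
| 5% | 10% | 0.95 × 0.10 = 9.5% |
| 10% | 20% | 0.90 × 0.20 = 18% |
| 10% | 30% | 0.90 × 0.30 = 27% |

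**4. What follows for the MTD?** Both rules were simulated. Assumptions: cohorts of three after the first DLT; the λ boundaries also used to escalate from 3 GBq, for which Table 3 gives no row; Table 3's elimination and level 1 stopping rows; stopping at 0 of 6; at most 18 patients; MTD by isotonic regression, closest to 30%. Ranges are across separate runs.

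| Assumed rates 3/6/9 GBq | Measure | Text | Table 3 |
|---|---|---|---|
| 5/10/20% | 9 GBq selected, trials with the event | 75% | 65–67% |
| 5/10/20% | Mean patients at 3 GBq, trials with the event | 2.0–2.1 | 5.7 |
| 5/10/20% | 9 GBq selected, all trials | 92.6% | 91.9% |
| 10/30/45% | 6 GBq selected, trials with the event | 65–66% | 60% |
| 10/30/45% | 6 GBq selected, all trials | 58.1% | 56.5% |

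The two scales agree: a 5 to 6 point difference in 27% of trials is 0.27 × 5 to 0.27 × 6, or about 1.4 to 1.6 points overall.

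**The case against.** The best defence is that the two paragraphs form a sequence. The second describes a one-patient run-in that ends at the first DLT, when the cohort is completed to three. The third then governs conduct from n = 3, and columns 1 and 2 are just generic output of n × λ. A second harmonising reading is that expanding means raising the cohort size from then on, in which case Table 3 does apply at 1 of 1. Either could be what was meant. But they lead to different actions, and neither is written down. The NA entries at n = 1 and n = 2 in the other rows also make it hard to treat the 1 in the de-escalation row as inert. That the article is condensed does not help, because it states both rules.

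The defence does limit the scope. A reader might extend the conflict to 9 GBq, since levels 2 and 3 share rows. The text does not support that: with levels 1 and 2 clean, level 3 already has a cohort of three, and if a DLT has occurred earlier and cohorts are then three, a one-patient decision at 9 GBq does not arise. A reader might also count 1 of 2. With cohorts of one or three and a pause only at the end of a cohort, two patients is not a planned decision point. Level 1 has no conflict, because its row shows NA there.

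A reader might also infer that BOIN's operating characteristics can attach to neither version. That is wrong: each rule is complete once chosen, both can be simulated, and the article quotes no operating characteristics that either would invalidate.

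**Conclusion.** The concern holds for one event: a DLT in the first 6 GBq patient after a clean single patient at 3 GBq. The article states two actions for it without precedence, and does not say whether Table 3 waits for a cohort of three. This rests on the text alone and needs no assumption about toxicity.

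The size does depend on assumed DLT rates. The article expects little added toxicity and cites grade 3 acute EBRT toxicity below 5%, so the lower end of the frequency range is closer to its own expectation; 27% needs a true rate of 30% at 6 GBq. When the event occurs, the next patients' activity is decided entirely by the rule followed, while MTD selection moves by roughly 5 to 10 points in the scenarios shown. Averaged over all trials, no dose's selection probability moved by more than about 1.6 points. The reason to act is an ambiguous safety decision. The documents do not support a claim that the design as a whole is compromised.

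**What to change.** Reconcile the second and third paragraphs of Dose escalation with Table 3, so that a DLT in the first patient at level 2 has one stated action. State the number of patients at which Table 3 is first applied, and mark as not applicable any column that is not a decision point. Which rule stands is for the sponsor and its safety committee; this review takes no position. Recruitment began in January 2022, so the clarification should also record whether the situation has already occurred and which rule was followed.

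Cost: a sentence, a small change to the table if needed, and a notice to sites. No extra patients.
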